### Treatment Allocation

#### Randomization

Participants will be randomly assigned (1:1) to either the aerobic-based exercise training (AT) group or the usual care (CON) group. The randomization sequence will be generated by a central, web-based randomization service http://www.randomization.net; permuted blocks of varying size will be employed to ensure balance over time. After baseline assessment, research personnel not involved in measurement or intervention will access the web-based randomization service to determine the group allocation.

#### Allocation Concealment

Recruitment and enrolment of participants will be managed by the research coordinator who will screen for study eligibility, obtain informed consent, and conduct baseline assessment. Following completion of baseline assessment, the research coordinator will access the web-based randomization service and the participant will be assigned a participant number and allocated to the intervention or the control group. Research personnel performing the outcome assessment and data analysis will be blinded to group allocation but it is not possible to blind participants and personnel delivering interventions to group allocation.

### Experimental Groups

#### Aerobic-Based Training (AT) Group

All AT group classes will be led by instructors certified to instruct seniors. Each 60-minute class will include a 10 minute warm-up, a target of 40 minutes of walking, and a 10-minute cool down. Class attendance will be recorded for each participant by the instructors throughout the six-month intervention period.

Over the six month intervention period, we will use three complimentary techniques to monitor and progress exercise intensity of the AT program. Each participant will:

1) Wear a heart rate monitor and will be asked to work initially at approximately 40% of his/her age specific target heart rate (i.e., heart rate reserve; HRR) and gradually progress to reach the target of 60% of HRR. Once the target of 60% of HRR is achieved, it will be sustained by the participant for the remainder of the intervention period;

2) Subjectively monitor the intensity of each workout using the Borg's Rating of Perceived Exertion (RPE) [49]. Participants will be gradually progressed to a target RPE of 14 to 15; and

3) Use the simple "talk" test [50,51]. Participants will be asked to initially walk at a pace where they can converse comfortably without effort and gradually progress to a pace where conversation requires a bit of effort.

In addition to the formal group classes, all individuals in the AT group will be given a pedometer to serve as both an incentive and reminder to partake in walking on a daily basis. Participants will be asked to record the number of steps each day. All pedometers will be returned to the study coordinator at the 6 month assessment session.

#### Usual Care (CON) Group

Participants in the CON group will receive educational material about vascular cognitive impairment and about stress management, healthful diet, and smoking. However, this group will not receive specific information regarding physical activity. Participants in the AT group will also be offered these educational materials.

### Adverse Events Monitoring

[name], in addition to a physician and statistician external to the research team, will review all adverse events reported in the study on a monthly basis. They will inform us to stop the study if the adverse events data are of sufficient concern.

### Statistical Analyses

As a primary objective of this study is to provide preliminary evidence of **efficacy **we will compare participants of the AT group who are compliant with the intervention (defined as attending 60% of the total exercise sessions) to the CON group rather than using an intention-to-treat analysis as would be appropriate in a pivotal clinical trial. In addition, no adjustment for multiple endpoints will be made since in a proof-of-concept study a Type II error is of more concern than a Type I error [52]. For each of the three primary endpoints (i.e., ADAS-Cog, EXIT-25, ADCS-ADL), the change from baseline to six months and 12 months will be assessed using an analysis of covariance model incorporating the baseline measurement. Observing a statistically significant difference on **any **of the three primary outcomes will be considered preliminary evidence of efficacy.

We will also report variances, co-variances, and effect sizes, as well as sampling feasibility (i.e., ease of recruitment, recruitment rate, withdrawal rate). This information will inform sampling for future trials.

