### Sample Size

Prior to launching a definitive randomized controlled trial, it is essential that the feasibility of conducting such a trial be demonstrated. A sample for a definitive study with multiple end-points and outcome variables will require several hundred participants and warrant a multi-site study. Given that no study has examined the effect of exercise on cognitive function in SIVCI, we have selected a sample size of 30 participants per group. Studies have suggested a standard deviation of change of 6 to 7 [27-29] in Alzheimer Disease Assessment Scale Cognitive (ADAS-Cog) scores among individuals with vascular cognitive impairment. We highlight that a recent exercise trial among seniors at risk for AD with ADAS-Cog as the primary outcome measure demonstrated an effect size of 0.60 [30]. Thus, assuming an alpha of 0.05, 30 participants per group will provide a power of 0.75 to 0.80. We estimate a drop-out rate of 10% during a 12-month period. Hence, we are aiming to recruit 35 participants per group (i.e., 70 participants in total) which will accommodate a conservative 15% drop-out rate.

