### Measurements

Baseline measurements will be obtained prior to randomization. There will be three measurement sessions: baseline, 6 months, and 12 months (Figure 1). Outcomes will be assessed by trained assessors blinded to group allocation.

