We will evaluate health related quality of life using the EuroQol 5D (EQ-5D) -- a preference-based generic utility instrument that provides weightings for quality adjusted life year (QALYs). QALYs are defined as the benefit of a health intervention in terms of time in a series of quality-weighted health states, in which the quality weights reflect the desirability of living in the state, typically from "perfect" health (weighted 1.0) to dead (weighted 0.0) [47]. QALYs are calculated based on the quality of life of a patient (measured using health utilities) in a given health state and the time spent in that health state. The EQ-5D captures 243 unique health states based on the following domains: 1) mobility; 2) self-care; 3) usual activities; 4) pain and 5) anxiety or depression. We will calculate QALYs using the health state utility values from the EQ-5D to determine if there is a statistically significant difference in the incremental cost per QALY change for participants receiving the aerobic-based training compared with those who are not.

5) Health Resource Utilization 

The health resource utilization questionnaire asks participants to report the following visits over a specified time period: 1) health care professionals; 2) admissions or visits to hospital; and 3) laboratory work. The health resource utilization questionnaire has been previously described and supported in previous studies [48]. We will estimate total health care related costs over the 12 months from a Canadian health care system perspective. Participants will be instructed to specify total health care expenditure and report the reason for each item. Additionally, participants will be instructed to report health care expenditure due to any adverse events associated with the aerobic-based training program; this is not anticipated to be a major cost driver. On a per participant basis, costs will be assigned to health care resource utilization using a fully allocated hospital cost model (for in-patient costs) and the British Columbia provincial guide to medical fees (for outpatient costs). Our base case analysis will consider the costs of all health care resource use and our sensitivity analyses will include only intervention related health care resource costs and a complete case analysis.

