### Economic Analysis

Our economic evaluation will explore incremental costs and health benefits comparing the aerobic-based training intervention with usual care using both cost effectiveness and cost utility analyses. A cost utility analysis is a specific type of cost effectiveness analysis where health benefits are measured using QALYs. The outcome of our cost effectiveness analysis is the incremental cost effectiveness ratio (ICER). By definition, an ICER is the difference between the mean costs of providing the competing interventions divided by the difference in effectiveness, where ICER = Δ Cost/Δ Effect [53]. We will determine the incremental cost of the aerobic-based training intervention per person experiencing a clinically significant improvement in cognitive performance relative to usual care. Further, for our cost utility analysis, we will estimate the incremental cost per quality adjusted life year gained (QALY). We will use a combination of imputation and bootstrapping to quantify uncertainty due to missing values and the finite study sample size^60 61^.

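### The 12-month ANCOVA of the primary outcomes, as written, makes no use of the 6-month score of a participant who leaves after month 6; a repeated-measures model would use it and remove a modest possible bias

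*Protocol article*

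**What the plan says.** The Measurements section sets the visits: "There will be three measurement sessions: baseline, 6 months, and 12 months". For each of the three primary endpoints, the Statistical Analyses section states that "the change from baseline to six months and 12 months will be assessed using an analysis of covariance model incorporating the baseline measurement". It names no covariate other than baseline and no method for a missing primary score. It does not say whether the two time points are fitted separately or together.

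The same section defines the comparison as AT participants who are "compliant with the intervention (defined as attending 60% of the total exercise sessions) to the CON group rather than using an intention-to-treat analysis".

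The Sample Size section says "We estimate a drop-out rate of 10% during a 12-month period". It powers the trial on 30 per group and recruits 35, "which will accommodate a conservative 15% drop-out rate". On that arithmetic, participants who withdraw are not counted in the analysed sample.

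**The concern.** An ANCOVA of change to month 12 needs a month-12 score. Without imputation, a person who comes at months 0 and 6 and is then lost falls out of the 12-month estimate. The 6-month score still enters the 6-month comparison, but it does not inform the 12-month one.

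That score carries information on how the person would probably have done at month 12. If people who have worsened by month 6 leave more often in one arm than in the other, the remaining participants in that arm look better than the arm did as a whole. Such loss in the control group hides part of a benefit. Such loss in the exercise group creates or enlarges one. The arms differ in contact (thrice-weekly classes against educational material) and participants know their allocation, so a different pattern of loss is possible, though no passage predicts it. The 12-month results also count towards efficacy in a trial that accepts significance on any one of three outcomes without adjustment for multiplicity.

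The 60% attendance rule is a different matter. Training ends at month 6, so a participant can meet that rule and be lost afterwards. This point would remain if everyone randomised were analysed.

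**Working it through.** **Inputs from the protocol article (Sample Size):** 35 recruited and 30 analysed per group; drop-out 10% expected and 15% allowed for; SD of ADAS-Cog change 6 to 7 (midpoint 6.5 used); effect size 0.60.

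**Assumptions not in the article:** correlation r of the 6- and 12-month changes, 0.5 to 0.7; share p lost after month 6, 5% to 15%; gap g in 6-month change between leavers and stayers in the selective arm, 0.5 to 1.0 SD.

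**Step 1, the plan's own figures.** 35 x 0.85 = 29.75, so 35 per group leaves about 30 after 15% loss. At 10% loss, 35 x 0.90 = 31.5 remain. So 3.5 to 5.25 people per arm may lack a 12-month score. The planned effect is 0.60 x 6.5 = 3.9 points.

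**Step 2, bias by formula.** Suppose loss depends on the 6-month change in one arm only. The mean 12-month change among that arm's stayers then differs from the mean of the whole arm by

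bias = p x r x g x SD.

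- Low end: 0.05 x 0.5 x 0.5 x 6.5 = 0.08 points.
- High end: 0.15 x 0.7 x 1.0 x 6.5 = 0.68 points.

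Simulation of this situation gives about 0.1 to 0.65 points. Against the planned effect, 0.1 / 3.9 = 3% and 0.65 / 3.9 = 17%. Changing the SD within 6 to 7 alters the points but not the formula's share, p x r x g / 0.60.

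**Step 3, a separate simulation.** 35 per arm, true difference -3.9 at both visits, SD 6.5, r = 0.6 and baseline SD 8 (both assumed). Drop-out after month 6 was weighted by exp(1 per SD of 6-month change). At nominal 10% and 15% loss, 4 and 5 of 35 leave each arm. Mean 12-month estimates:

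| Loss after month 6 | ANCOVA, observed scores | Model using 6-month score | Last score carried forward |
|---|---|---|---|
| Random, 10% / 15% | -3.89 / -3.89 | -3.90 / -3.90 | -3.90 / -3.91 |
| Equally selective in both arms | -3.85 / -3.90 | -3.86 / -3.90 | -3.86 / -3.90 |
| Selective in control only | -3.50 / -3.36 | -3.93 / -3.89 | -4.18 / -4.19 |

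With complete data, the control-only rows gave -3.93 and -3.90, so the bias is 0.43 and 0.54. The formula with g = 1.0 gives (4/35) x 0.6 x 6.5 = 0.45 and (5/35) x 0.6 x 6.5 = 0.56, in agreement.

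**Step 4, scale.** With 30 per arm the unadjusted standard error of the difference is 6.5 x sqrt(2/30) = 1.68 points. A bias of 0.1 to 0.65 is 0.06 to 0.39 of one standard error.

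**The case against.** The strongest reply is that the article does not say what happens to a missing primary score. It mentions neither complete cases nor separate fits, ANCOVA can be combined with imputation, and such detail is commonly left to an analysis plan that is not shown here. That stands, and it is why the point is conditional. What remains is that the article does name a model, with baseline as its only stated covariate, and that the sample size does not count on withdrawals. Followed as written, that model leaves the 6-month score unused at month 12.

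It is also true that progressive disease alone creates no bias. Decline that drives people out equally in both arms leaves the difference nearly unchanged, as the second row of the table shows. The simulations take all 35 per arm and do not apply the attendance rule, so they illustrate the mechanism and do not forecast this trial.

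A reader might infer three stronger points that the documents do not support.

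- **A contradiction with the economic analysis.** The Economic Analysis section says "We will use a combination of imputation and bootstrapping to quantify uncertainty due to missing values and the finite study sample size", and the health resource item under Secondary Outcomes says "our sensitivity analyses will include only intervention related health care resource costs and a complete case analysis". Both concern the economic evaluation only. Naming a method there does not fix the opposite one for the primary outcomes.
- **Two inconsistent cognitive effects.** The cost-effectiveness ratio counts people with a clinically significant improvement, while the efficacy analysis compares mean change. These are different quantities and would differ with complete data.
- **A larger bias.** Figures of 0.66 to 0.94 points arise only if about 16.5% of one arm leave after month 6, selectively in that arm alone. That exceeds both drop-out rates in the Sample Size section.

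**Conclusion.** The point holds in a limited form. Unless missing scores are imputed, the stated 12-month ANCOVA leaves out participants lost after month 6 and does not use their 6-month scores. Under selective loss in one arm, the 12-month ADAS-Cog difference is biased by about 0.1 to 0.65 points, in either direction depending on the arm. That range rests on the assumed loss, correlation and strength of selection, none of which the article gives beyond its overall drop-out rates. The same mechanism applies to EXIT-25 and ADCS-ADL, for which the article gives no SD, so no size can be put on it. The bias is smaller than the sampling error of a trial this size, but it is avoidable with scores that will already have been collected. It is an improvement to the analysis and not an error that invalidates the trial.

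**What to change.** In the Statistical Analyses section, specify for each primary outcome one baseline-adjusted repeated-measures model: arm, visit, arm by visit, baseline and baseline by visit, with unstructured covariance, fitted to all available 6- and 12-month scores. Read the 6-month and 12-month differences from it, and report the ANCOVA of observed scores as a sensitivity analysis. Do not carry the last score forward: in the simulation this overstated the effect (-4.18 and -4.19 against -3.9).

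The cost is a change of wording and slightly more analysis work, with no new data or participants. The model assumes that scores are missing at random given baseline, arm and the 6-month score. It cannot recover people who leave before month 6 and so have no follow-up score.

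Leave the economic evaluation as it is. Tying its cognitive effect to the participants in the efficacy analysis would carry the 60% attendance rule into an analysis for which the article states no such restriction.

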### Economic Analysis

Our economic evaluation will explore incremental costs and health benefits comparing the aerobic-based training intervention with usual care using both cost effectiveness and cost utility analyses. A cost utility analysis is a specific type of cost effectiveness analysis where health benefits are measured using QALYs. The outcome of our cost effectiveness analysis is the incremental cost effectiveness ratio (ICER). By definition, an ICER is the difference between the mean costs of providing the competing interventions divided by the difference in effectiveness, where ICER = Δ Cost/Δ Effect [53]. We will determine the incremental cost of the aerobic-based training intervention per person experiencing a clinically significant improvement in cognitive performance relative to usual care. Further, for our cost utility analysis, we will estimate the incremental cost per quality adjusted life year gained (QALY). We will use a combination of imputation and bootstrapping to quantify uncertainty due to missing values and the finite study sample size^60 61^.

### Time Frame

Recruitment will commence in December 2009. Final follow-up assessment is expected to conclude in February 2012.

## Discussion

Although exercise therapy holds promise for delaying the onset and slowing down the progression of both cognitive and functional decline, very few randomized controlled trials of exercise have been conducted in populations at high-risk for dementia [30]. This research will be an important first step in quantifying the effect of an exercise intervention on cognitive and daily function among seniors with SIVCI, as vascular cognitive impairment is the second most common cause of dementia in older adults [1-4]. Exercise has the potential to be an effective, inexpensive, and accessible intervention strategy with minimal adverse effects. Retarding the rate of cognitive decline among seniors with SIVCI could preserve independent functioning and quality of life in this population. This, in turn, could lead to reduced health care utilization costs and avoidance of early institutional care. Delaying the onset or retarding the progression of dementia by only one year would reduce the number of clinical cases of dementia by 9.2 million by 2050 in the US alone [54].

Our interdisciplinary research team will use a multi-pronged approach to explore the utility of aerobic-based exercise training among seniors with mild SIVCI. The impact of our proposed work may be significant for seniors with mild SIVCI.
